### Participants

#### Study 1

We based our calculations on an approximate population size of 60,000 young individuals supported throughout the previous year (Year N-1) across the entire territory. The margin of error was set at 5%, with a confidence level of 95%. We applied Cochran’s formula (Z² × p × (1-p) / E²) to determine the required sample size. Accordingly, the sample size necessary for this cross-sectional study is 382 respondents.

#### Study 2

We will base our qualitative study on a sample of 30 young volunteers recruited independently of the cross-sectional study, following the procedures outlined below. However, participant inclusion will continue until data saturation is reached. Data saturation will be considered achieved when the main themes emerge, meaning that all relevant themes necessary to address the research questions have been identified in the collected data.

#### Study 3

For this study, we estimate a strong effect size of 0.7 (Cohen’s d) with a significance level of 0.05. Based on these parameters, and using the software G*Power 3.1, we determined that 55 participants would be required for each group modality, resulting in a total of 165 participants. To account for an estimated 10% dropout rate, we will include 182 young individuals in the study.

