The longitudinal study will follow the same inclusion criteria as the qualitative study (Study 2). However, participation in the group sessions is open to all volunteers for each session, regardless of whether they are substance users. Informed consent will be systematically obtained before each session, ensuring fully informed participation. Promotion of the groups will be conducted through widespread dissemination of informational posters, email communications via the management of the partner structures, and during informational meetings. A follow-up meeting will be organized 15 days later to conduct the initial T0 evaluation with the volunteers.

The “Well-Being coffee group” intervention is implemented in several formats (see Fig. 1). Some groups will take place in person, others via videoconference, all conducted by the same psychologist throughout the sessions. Additionally, a control group will consist of participants who underwent the initial evaluation (T0) but did not attend any sessions. The inclusion of this control group allows for the assessment of changes in psychological and behavioral outcomes over time, comparing those who received the intervention to those who did not. The choice of this comparator was made based on feasibility and ethical considerations, ensuring that participants were not deprived of potential care while maintaining an adequate framework for evaluating the intervention’s effects. Across all formats, participation is voluntary, following a prior information phase and the signing of an informed consent form. Participants will complete standardized evaluation questionnaires at multiple time points (T0, T1, T2, T3).

The discussion groups aim to provide a supportive and open space for free expression. Their objective is to allow participants to articulate their thoughts, emotions, and personal experiences, as well as those evoked by group discussions on various themes, including identity, substance use, migratory experiences, and mental health. The impact of the intervention will be assessed regularly using standardized tools to measure levels of anxiety, depression, and changes in attitudes and willingness to seek help. Finally, a global satisfaction scale will be used at the end of the sessions to collect participants’ subjective feedback on their experiences within the groups (see Fig. 1).

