### Data analysis

#### Study 1

The research team will conduct statistical analyses using R. The cross-sectional study will characterize the study population through descriptive and multivariate analyses (e.g., Chi-square/Fisher’s exact tests, correlation tests, ANOVA, etc.). We will adhere to the STROBE guidelines for epidemiological studies [58]. A significance level of 0.05 will be applied for statistical analysis.

#### Study 2

A thematic analysis of the data from the semi-structured interviews will be conducted using NVivo 15 software. Moreover, the findings from the Rorschach test will be analyzed using a methodology for interpreting projective material [48], with the aim of highlighting underlying psychic processes, particularly those related to attachment dynamics early traumas, the defensive mechanisms of participants. Additionally, the interviews reported from the AAI assessment will be coded by MN and AF under the supervision of a certified reliable coder [name] using the Adult Attachment Scoring and Classification System [49].

#### Study 3

For the group intervention, a Bonferroni correction will be applied to all *p*-values in t-tests. Cronbach’s alpha will be used to assess the reliability of the scales. Various analyses will be conducted to evaluate pre- and post-intervention effects as well as dose-response effects, including Student’s t-tests, repeated-measures ANOVA, and linear regression.

Primary and secondary outcomes will be analyzed using linear mixed models, incorporating a random group effect if estimation permits. The primary outcome measure is the variation in the total score on the ATSPPH-S at 9 months, calculated using dimensional scoring algorithms. Changes in the primary outcome and the relative effectiveness of the four intervention modalities will be assessed using mixed regression models, utilizing all available data while accounting for participant, time, and group levels. The underlying distribution for the mixed regression model will be determined based on residual distribution.

Per-protocol analyses will also be performed to test robustness. ANCOVA analyses may be conducted as needed to control for confounding variables that could influence the results. If data distribution is non-parametric, analyses such as Mann-Whitney, Wilcoxon, and Kruskal-Wallis tests will be employed.

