Missing data will be reported and managed using appropriate imputation methods depending on their proportion and classification (MCAR, MAR or MNAR). However, if the proportion of missing data is very large (> 40%), we will present only the results of the complete case analysis [59].

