### Safety considerations

No adverse effects are expected. The questionnaires selected for this study have widely been used in previous research with self-administrated protocols. Meanwhile, the semi-structures interviews from study 2 and focus groups from study 3 may bring up difficult life events. In cases where participation leads to distress or emotional discomfort, participants will receive support and compassionate guidance from the investigator/psychologist conducting the interview, as well as during an individual debriefing following the group sessions. If an urgent need for care is identified, participants will be referred to appropriate socio-medical services for further support.

The findings of the study will be published and shared with the scientific community including scientific publications, conference posters and oral presentations in national and international conferences.

Withdrawal from any phase of the study will be considered if participants revoke their consent during data collection, if they discontinue attendance at research interviews, or if they cease participation in group sessions. Withdrawal is entirely voluntary and will not result in any consequences, ensuring adherence to ethical research principles.

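### The complete-case-only rule above 40% missing data conflicts, as written, with the all-available-data mixed model for Study 3's primary outcome

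*Protocol article*

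**What the plan says.** All references are to the protocol article.

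- **Primary outcome (Data analysis, Study 3).** "The primary outcome measure is the variation in the total score on the ATSPPH-S at 9 months".
- **Primary analysis (same section).** Change in that outcome is assessed with "mixed regression models, utilizing all available data while accounting for participant, time, and group levels".
- **Missing data (end of the same section).** Missing data are to be "managed using appropriate imputation methods depending on their proportion and classification (MCAR, MAR or MNAR"). The next sentence is the exception: "if the proportion of missing data is very large (> 40%), we will present only the results of the complete case analysis". The text does not say what the 40% is a proportion of.
- **Assessments (Procedures, Study 3).** "Participants will complete standardized evaluation questionnaires at multiple time points (T0, T1, T2, T3"). The 9-month outcome is taken here to be the T3 score.
- **Withdrawal (Safety considerations).** Withdrawal is considered, among other reasons, for participants "if they cease participation in group sessions".
- **Planning (Participants, Study 3).** "we estimate a strong effect size of 0.7" (Cohen's d), with 10% dropout and 182 to be included.

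**The concern.** The two statements in the Data analysis section cannot both govern the primary result once missingness passes 40%. A mixed model on all available data keeps a participant with T0, T1 and T2 scores but no T3 score. A complete-case analysis removes that participant, and the word "only" leaves no room to show the mixed model beside it.

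The switch also runs in an unhelpful direction. A likelihood-based mixed model needs no imputation and is valid when loss depends on scores already observed. A complete-case comparison of change generally needs more: loss must not be related to change in a way that differs between arms. The rule adopts the stronger assumption when the most data are missing, and makes no exception for the MAR and MNAR cases named in the sentence before it.

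Different loss mechanisms across arms are plausible here. Attendance is voluntary and the groups are open. Ceasing to attend sessions is a ground for withdrawal that can apply only to people who attended, and the control group is defined as those who attended none. If the rule came into play, the reported effect would describe those who stayed, and the estimate could jump at the threshold. With the 40% undefined, whether the rule applies could be settled after the data are seen.

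**Working it through.** **1. The plan's own figures.** The 40% is a rule with no derivation to reproduce. The planned size is 3 × 55 = 165, and 165 × 1.10 = 181.5, rounded to 182. The 55 per group is reproduced by a two-sided t-test at 0.05 with d = 0.7 and 95% power (0.9499 at 54, 0.9533 at 55). The article does not state the power; 95% is inferred. At exactly 40% missing, 182 × 0.60 = 109.2, so about 109 participants would be complete. The other 73 or so, with whatever earlier scores they gave, would be dropped by a complete-case analysis and kept by the mixed model.

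**2. Assumptions for the bias calculation (none is from the article).** Four visits, each score with SD 1; correlations 0.7, 0.6 and 0.5 at lags 1, 2 and 3; no true effect; 45% missing at T3 in each arm. In the intervention arm the log-odds of staying rise by 1 per SD of a driver D. In controls loss is random, or follows the same mechanism where stated.

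**3. Formula.** Let C = T3 − T0. With normal scores, the complete-case bias in one arm is

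bias = [Cov(C, D) / SD(D)] × m,

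where m is the mean of the standardised driver among stayers. Setting logit P(stay) = a + z with P(stay) = 0.55 gives, by numerical integration, a = 0.243 and m = 0.372.

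**4. Numbers put in.**

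| Driver of loss, intervention arm only | Cov(C, D) | SD(D) | Bias of complete-case change |
|---|---|---|---|
| T2 − T0 (non-improvers leave) | 0.7 − 0.5 − 0.6 + 1 = 0.6 | √(2 × 0.4) = 0.894 | 0.671 × 0.372 = +0.25 |
| T2 score | 0.7 − 0.6 = 0.1 | 1 | +0.04 |
| T0 score | 0.5 − 1 = −0.5 | 1 | −0.19 |
| T3 − T0 itself (unseen) | 1 | 1 | +0.37 |

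If the same mechanism acts in both arms, the two arm-level biases cancel and the difference is about 0.

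**5. Available-data estimate.** Regressing T3 on T0 to T2 among stayers and averaging over everyone (a stand-in for the mixed model) gave a bias of about 0 in the first three rows. In the fourth row it was about +0.20, against +0.37 for complete case.

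**6. At the planned arm size.** With 55 per arm and the first mechanism, two simulations of 3000 runs gave complete-case bias of about +0.24 SD and false-positive rates of 14.6% and 16%. When loss was completely at random there was no material bias, only lost precision (SD of the estimate 0.26 v 0.23).

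**7. A second scenario.** A true difference of 0.70, equal correlation between visits of 0.5 or 0.7, and loss depending on the last observed score in one arm. With 47% to 61% missing, the complete-case difference in change was 0.60 to 0.66, a bias of −0.04 to −0.10. The available-data likelihood fit stayed between 0.68 and 0.71.

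**The case against.** **The sentence may be only an imputation rule.** It follows directly on the sentence about imputation and names no model. A fair reading is that above 40% nothing is imputed while the mixed model is still fitted to the observed data. A reader might infer that the authors have decided to abandon the mixed model; the text does not establish that intention. What stands is that the sentence, followed literally, has that effect, so it has to be reconciled with the primary analysis on either reading.

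**The bias depends on the mechanism.** This stands. A reader might infer that complete case would inflate the intervention effect by a quarter of an SD. That is one end of the range: it needs non-improvers to leave the intervention arm while controls leave at random. Other mechanisms give nearly nothing or the opposite sign.

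**The mixed model is not a cure.** This also stands. Under loss that depends on the unseen 9-month change in one arm, both estimates are biased. Declining to present heavily model-dependent imputed results at high missingness is a recognisable caution, though allowing only complete case goes too far.

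**The rule is a contingency.** The planned dropout is 10%, a quarter of the threshold. Nothing in the article shows that loss will pass 40%, so it should not be read as expected. This lowers the severity but does not make the rule sound.

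**The article is condensed.** The lack of a detailed MNAR sensitivity analysis is no fault here, since an article may leave it to the full protocol or analysis plan. The source cited for the rule was not available, and nothing here rests on it.

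**Conclusion.** The point holds at moderate severity. As written, the rule above 40% conflicts with the stated all-available-data analysis ("utilizing all available data while accounting for participant, time, and group levels") and discards usable T0 to T2 data. At 45% missing, with no true effect and the assumed correlations, the resulting bias in change ranges from about −0.19 to +0.25 SD when intervention-arm loss depends on observed scores and control loss is random. The upper end is about a third of the planning effect (0.25 / 0.7 = 0.36). The bias is about 0 when the mechanism is the same in both arms.

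In these observed-score scenarios the available-data estimate stayed near 0. That result assumes a model flexible enough in its visit means and correlations, and loss that depends only on observed scores. The direction and size of any bias in the actual trial cannot be predicted from the document. The firm conclusions are the conflict in the text, the undefined 40%, and the fact that the literal rule requires the stronger assumption where missingness is highest.

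**What to change.** Replace the sentence with wording to this effect: *The mixed model on all available data remains the primary analysis of Study 3 at any level of missingness. A complete-case analysis is presented as a sensitivity analysis only. If more than 40% of 9-month ATSPPH-S scores are missing, the Study 3 result is interpreted as exploratory.*

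This settles the conflict, defines the 40%, and keeps the caution the authors may have intended. If they meant only that they would not impute above 40%, the same wording serves, with a clause saying so.

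The cost is one sentence of wording and a more cautious conclusion if loss is high. No new data are needed. The article's Trial status section describes recruitment as ongoing and requires ethics committee approval before a substantial modification, so the change should be made before outcome data are examined and documented as that section describes.

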### Ethical considerations

We obtained approval from the Committee for the Protection of Persons (CPP) Ile de France VI in November 2024 to conduct this study, classified as a Minimal Risk Interventional Research (RIPH 2) study, and registered under number ID-RCB: 2024-A01534-43.

The ATICC research project is also registered in the data processing registry of the University of Lorraine under number 2024 − 358 of 25/07/2024, and adheres to the Reference Methodology MR-001, a regulatory framework defined by the French Data Protection Authority or National Commission on Informatics and Liberty (CNIL) for research involving personal data in the health domain. These registrations ensure that the processing of participants’ personal data complies with ethical and legal standards for data protection, in accordance with the General Data Protection Regulation (RGPD) and the internal guidelines of the University of Lorraine. Any identifying information will be removed before data analysis to maintain anonymity.

### Data monitoring and management

No data monitoring committee has been appointed, as data monitoring responsibilities are shared among the research team members. Data entry will be verified twice to ensure accuracy, and data quality will be assured through range checks.

### Safety considerations

No adverse effects are expected. The questionnaires selected for this study have widely been used in previous research with self-administrated protocols. Meanwhile, the semi-structures interviews from study 2 and focus groups from study 3 may bring up difficult life events. In cases where participation leads to distress or emotional discomfort, participants will receive support and compassionate guidance from the investigator/psychologist conducting the interview, as well as during an individual debriefing following the group sessions. If an urgent need for care is identified, participants will be referred to appropriate socio-medical services for further support.

The findings of the study will be published and shared with the scientific community including scientific publications, conference posters and oral presentations in national and international conferences.

Withdrawal from any phase of the study will be considered if participants revoke their consent during data collection, if they discontinue attendance at research interviews, or if they cease participation in group sessions. Withdrawal is entirely voluntary and will not result in any consequences, ensuring adherence to ethical research principles.

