## Methods/design

This research project is therefore structured around three complementary phases of study (Table 1), each based on a distinct methodological approach:

A **cross-sectional study (study 1)** that relies on a quantitative approach, conducted through the dissemination of online standardized questionnaires and scales (see: Measures) to young adults residing in partner structures at both regional and national levels. Its objective is to identify factors associated with addictive behaviors and to explore the links between trauma, migratory trajectories, food insecurity, psychological distress and perceived representations and barriers to accessing psychological care. These tools enable the rigorous collection of quantitative data and a multidimensional assessment to model the relationships between factors associated with the psychological and social challenges faced by this population. This study provides insights into general statistical trends.A **qualitative study (study 2)** adopting an exploratory perspective and aiming an in-depth understanding of the representations, subjective experiences, and individual and relational dynamics associated with addictive behaviors and trauma. The qualitative study builds upon the findings of Phase 1 by collecting clinical insights that provide a deeper understanding of the subjective dynamics of participants dealing with substance use issues and the obstacles encountered in their life trajectories that shape their relationship with care services.A **longitudinal study (study 3)** structured around a group intervention called the “Well-Being coffee group”, which operates as an open group (8 to 12 participants per session), conducted over six sessions, each lasting 1.5 to 2 h, held in the evening (6–8 PM) once a month for six months. Participation is voluntary for young residents in THP. The study aims to evaluate the impact of this group discussion format on participants’ psychological well-being, their perceptions of mental health, and their access to care.

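### The withdrawal rule treats stopping group sessions as a ground for leaving the study, which risks losing 9-month scores in the intervention formats only

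*Protocol article*

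**What the plan says.** Safety considerations gives one withdrawal rule for all three studies. It opens with "Withdrawal from any phase of the study will be considered if participants revoke their consent during data collection" and adds "if they discontinue attendance at research interviews, or if they cease participation in group sessions". The next sentence says that leaving is the participant's free choice and carries no penalty.

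The rest of Study 3 is built around voluntary, irregular attendance:

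- Methods/design describes an open group "conducted over six sessions, each lasting 1.5 to 2 h, held in the evening (6–8 PM) once a month for six months".
- Procedures, Study 3 says that "participation in the group sessions is open to all volunteers for each session". Controls are "participants who underwent the initial evaluation (T0) but did not attend any sessions". Participants are to complete questionnaires at T0, T1, T2 and T3.
- Data analysis, Study 3 sets the primary outcome as change in the ATSPPH-S total score at 9 months, analysed by mixed models on all observations. It adds per-protocol analyses as a robustness check, and other analyses to "evaluate pre- and post-intervention effects as well as dose-response effects".
- The closing paragraph of Data analysis plans imputation according to the amount and type of missingness, with complete-case results only above 40% missing.
- Participants, Study 3 allows for 10% dropout.

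**The concern.** Stopping an intervention and leaving a study are different events, and the rule does not distinguish them. In a group that people may join session by session, attending once or twice and then stopping is an expected pattern. The dose-response analysis needs outcomes from those people, and the primary model needs their later scores.

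The rule is also asymmetric. A person with a T0 who attends nothing is followed as a control, whereas a person who attends once and stops meets a ground for withdrawal. Controls cannot cease sessions, so any loss from this clause falls on the intervention formats alone.

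The primary outcome is attitude toward seeking psychological help. Leaving a psychologist-led discussion group is plausibly related to that attitude, so loss related to the outcome is a realistic possibility. If those who stop are no longer followed, the main and per-protocol analyses also converge and the robustness check loses value. No later analysis plan can recover scores that were never collected.

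**Working it through.** **The plan's own figure.** Inputs from Participants, Study 3: d = 0.7, alpha 0.05, 55 per modality, 165 in total, 182 after 10% dropout. Power and sidedness are not stated. A two-sided two-sample t-test (noncentral t) needs 34, 44 or 55 per group at power 0.80, 0.90 or 0.95, so 55 matches an inferred power of 0.95. Then 3 × 55 = 165 and 165 × 1.10 = 181.5, or 182. Dividing by 0.90 gives 184, a difference of 2 that does not matter here.

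**Assumptions for what follows.** The documents give no cessation rate. I assume three equal groups of 182/3 = 60.7, one of them the control group, with 10% loss in controls (60.7 × 0.90 = 54.6). Everyone who ceases in an intervention format is assumed lost.

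**Dropout allowance.** At 30% loss in both formats, overall loss is (30 + 30 + 10)/3 = 23.3%. At 40% it is (40 + 40 + 10)/3 = 30%. Both exceed 10%.

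**Power, one format against control (d = 0.7, two-sided 0.05).**

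| Loss in format | n in format | n in control | Power |
|---|---|---|---|
| 10% | 54.6 | 54.6 | 0.952 |
| 20% | 48.5 | 54.6 | 0.940 |
| 30% | 42.5 | 54.6 | 0.923 |
| 40% | 36.4 | 54.6 | 0.899 |
| 50% | 30.3 | 54.6 | 0.863 |

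Between two formats that both lose 30% or 40%, power is 89% or 84%. Those two figures do not apply to the control comparison.

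**Bias, simple bound.** Let q be the share of a format that stops and is lost, and g the amount in SD by which stayers exceed stoppers on 9-month change. The full mean is (1 − q)·m + q·(m − g) = m − qg, where m is the stayers' mean. The observed mean is therefore too high by q × g. For g from 0.2 to 0.7:

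- q = 10%: 0.02 to 0.07 SD
- q = 30%: 0.06 to 0.21 SD
- q = 40%: 0.08 to 0.28 SD

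If stoppers did better than stayers, the sign reverses.

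**Bias, by mechanism.** Illustrative simulation: true effect 0, 60 per arm, 2,000 runs, about 31% loss in the intervention arm only, complete cases adjusted for baseline.

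- Stopping depends on the observed baseline score: bias about 0.00 SD, type I error 0.047.
- Stopping depends on an unobserved trait related to the outcome: bias about 0.10 SD, type I error about 0.10.

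**The 40% fallback.** If the threshold is read over all participants, it is crossed when (2q + 0.10)/3 > 0.40, that is q > 0.55. If it is read within a format, it is crossed at q > 0.40. The article does not say which reading applies.

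**The case against.** A reader might infer that every low attender loses the 9-month score and that the primary, dose-response and control comparisons are therefore biased. The documents do not support that, for these reasons:

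- The verb in "Withdrawal from any phase of the study will be considered if participants revoke their consent during data collection" can mean that withdrawal is deemed or only contemplated. The following sentence calls withdrawal voluntary, which fits badly with automatic removal.
- Ceasing is not the same as intermittent attendance, and the article does not define it for an open group.
- No section says that T1 to T3 collection stops when sessions stop. Procedures ties the questionnaires to participants, not to attendance, and non-attending controls are followed.
- Scores already collected stay in the mixed model, which is valid if missingness depends on observed data. Imputation is also planned, and per-protocol analysis is secondary.
- The clause sits under a safety heading, covers three studies at once, and may condense fuller text.

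All of this stands against the strong reading. It does not remove the point. The current text names ceasing sessions as a withdrawal ground without qualification, and nothing says that follow-up continues. Someone who stops after one or two monthly sessions and is withdrawn may contribute only T0, which leaves the model little with which to explain the missing score.

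It is also fair to say that the control comparison is already self-selected, since controls are people who chose not to attend. The clause adds a separate, avoidable distortion, and correcting it does not cure the self-selection.

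**Conclusion.** The point holds as a conflict in the text with a conditional consequence. The withdrawal clause does not separate stopping the intervention from leaving follow-up. If it is applied as written, it risks attendance-related loss of the 9-month ATSPPH-S in the intervention formats only, against the T0 to T3 schedule and the planned analyses.

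The main harm is possible bias, whose size and direction depend on why people stop. Loss of power is not a material problem against controls at d = 0.7. The 10% allowance is doubtful rather than refuted, because the documents give no cessation rate. All the sizes shown rest on assumed loss rates, the three-group split, and withdrawal meaning no further assessment. That the comparisons are in fact biased cannot be concluded from the article.

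**What to change.** Reconcile Safety considerations with Procedures and Data analysis for Study 3 by stating that:

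1. ceasing group sessions is not withdrawal from the study;
2. the T1, T2 and T3 questionnaires are still requested from every participant with a T0, unless that person revokes consent to data collection;
3. the number of sessions attended is recorded as an exposure variable;
4. all T0 participants stay in the primary mixed-model analysis set.

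Participants remain free to stop sessions or to revoke consent at any time. The cost is a wording amendment, with the committee approval that Trial status requires if it counts as substantial, and sending existing self-administered questionnaires to people who stop, as is already needed for controls. Trial status gives recruitment as running from January to December 2025, so the change should be made promptly: 9-month scores not requested on time cannot be recovered.
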